#### **Pregnancy Reporting by Lead Principal Investigator to Celgene**

For lenalidomide pregnancies and suspected pregnancies (including a positive pregnancy test regardless of age or disease state) of a female subject occurring while the subject is on lenalidomide, or within 28 days of the subject's last dose of lenalidomide, are considered immediately reportable events. Lenalidomide is to be discontinued immediately and the subject instructed to return any unused portion of the lenalidomide to the investigator. The pregnancy, suspected pregnancy, or positive pregnancy test must be reported to the Lead Principal Investigator who will inform Celgene immediately using the Pregnancy Reporting Form provided by Celgene or an approved equivalent form. The exposure of any pregnant female (e.g., caregiver or pharmacist) to lenalidomide is also an immediately reportable event.

The female subject should be referred to an obstetrician-gynecologist, preferably one experienced in reproductive toxicity for further evaluation and counseling.

The Lead Principal Investigator will follow the female subject until completion of the pregnancy, and must notify Celgene immediately about the outcome of the pregnancy (either normal or abnormal outcome).

If the outcome of the pregnancy was abnormal (e.g., spontaneous or therapeutic abortion), the Investigator should report the abnormal outcome as an AE. If the abnormal outcome meets any of the serious criteria, it must be reported as an SAE within 24 hours of the investigator's knowledge of the event using the SAE Report Form, or MedWatch Form.

All neonatal deaths that occur within 28 days of birth should be reported, without regard to causality, as SAEs. In addition, any infant death after 28 days that the Investigator suspects is related to the in utero exposure to the lenalidomide should also be reported within 24 hours of the investigator's knowledge of the event using the SAE Report Form, or approved equivalent form.

If a female partner of a male subject taking investigational product becomes pregnant, the male subject taking IP should notify the investigator, and the pregnant female partner should be advised to call their healthcare provider immediately.

If a pregnancy related event is reported in a female partner of a male subject, the investigator should ask if the female partner is willing to share information with Celgene Drug Safety and allow the pregnancy related event to be followed up to completion.

The Lead Principal Investigator will inform Celgene immediately, using the Pregnancy Reporting Form provided by Celgene or an approved equivalent form, of any information related to pregnancies or suspected pregnancies (including a positive pregnancy test regardless of age or disease state) occurring in partner of patients while the patients are still treated with lenalidomide or within 28 days of the Patients' last dose of lenalidomide.

## **Overdose**

Overdose, as defined for this protocol, refers to lenalidomide, carfilzomib, daratumumab and dexamethasone dosing only.

On a per dose basis, an overdose is defined as the following amount over the protocol-specified dose of lenalidomide, carfilzomib, daratumumab and dexamethasone assigned to a given patient, regardless of any associated adverse events or sequelae.

- PO any amount over the protocol-specified dose
- IV 10% over the protocol-specified dose

On a schedule or frequency basis, an overdose is defined as anything more frequent than the protocol required schedule or frequency.

On an infusion rate basis, an overdose is defined as any rate faster than the protocol-specified rate. Complete data about drug administration, including any overdose, regardless of whether the overdose was accidental or intentional, should be reported in the case report form.

### **Pregnancy Reporting by Lead Principal Investigator to Amgen**

Report Pregnancy and potential infant exposure including lactation, within ten (10) calendar days of the Lead Principal Investigator awareness. Provide to Amgen the SAE reports associated with pregnancy.

Subjects, spouses, or partners will be followed through the outcome of the pregnancy.

If the outcome of the pregnancy meets a criterion for immediate classification as an SAE—spontaneous abortion (any congenital anomaly detected in an aborted fetus is to be documented), stillbirth, neonatal death, or congenital anomaly—the treating investigator should repeat the procedures for expedited reporting of SAEs as outlined above.

### **Pregnancy Reporting by Lead Principal Investigator to Janssen**

All initial reports of pregnancy must be reported to Janssen Scientific Affairs, LLC by the Principal Investigator within 24 hours of becoming aware of the event using the Serious Adverse Event Form. Abnormal pregnancy outcomes (e.g. spontaneous abortion, fetal death, stillbirth, congenital anomaly, ectopic pregnancy) are considered serious adverse events and must be reported using the Serious Adverse Event Form.

Because the effect of the Janssen medicinal product on sperm is unknown, pregnancies in partners of male subjects exposed to a Janssen medicinal product will be reported by the Lead Principal Investigator within

24 hours of their knowledge of the event using the Serious Adverse Event Form. Depending on local legislation this may require prior consent of the partner.

Follow-up information regarding the outcome of the pregnancy and any postnatal sequelae in the infant will be required.

## **9 INVESTIGATIONAL MEDICINAL PRODUCT**

### **9.1 Carfilzomib**

#### **9.1.1 Description**

Carfilzomib is a synthetic small molecule peptide bearing the chemical name (2S)-N-((S)-1-((S)-4-methyl-1-((R)-2-methyloxiran-2-yl)-1-oxopentan-2-ylcarbamoyl)-2-phenylethyl)-2-((S)-2-(2-morpholinoacetamido)-4-phenylbutanamido)-4-methylpentanamide. The molecular formula is C40H57N5O7 and the molecular weight is 719.91. It specifically functions as an inhibitor of the chymotrypsin-like activity of the 20S proteasome, which leads to the accumulation of protein substrates within the cell and induction of apoptosis.

#### **9.1.2 Formulation**

Carfilzomib for Injection will be provided as a lyophilized powder which, when reconstituted, contains 2 mg/mL isotonic solution of carfilzomib Free Base in 10 mM sodium citrate buffer (pH 3.5) containing 10% (w/v) sulfobutylether--cyclodextrin (SBE--CD, Captisol®).

#### **9.1.3 Storage**

Lyophilized Carfilzomib for Injection must be stored at 2–8°C under the conditions outlined in the separate Pharmacy Manual, in a securely locked area to which access is limited to appropriate study personnel.

#### **9.1.4 Accountability**

Amgen, Inc. and the Site Investigator will maintain records of each shipment of investigational product. The records will document shipment dates, method of shipment, batch numbers, and quantity of vials contained in the shipment. Upon receipt of the investigational product, the designated recipient at the study site will inspect the shipment, verify the number and condition of the vials, and prepare an inventory or drug accountability record.

Drug accountability records must be readily available for inspection.

Empty and partially used vials should be accounted for and destroyed at the study site in accordance with the internal standard operating procedures. Drug destruction records must be readily available for inspection.

Only sites that cannot destroy unused drug on-site will be required to return their unused supply of investigational product.

## **9.2 Lenalidomide**

### **9.2.1 Description**

Lenalidomide, a thalidomide analogue, is an immunomodulatory agent with anti-angiogenic and anti-neoplastic properties. The chemical name is 3-(4-amino-1-oxo 1, 3-dihydro-2H-isoindol-2-yl) piperidine-2, 6-dione. The empirical formula for lenalidomide is C13H13N3O3, and the gram molecular weight is 259.3.

Lenalidomide is off-white to pale-yellow solid powder. It is soluble in organic solvent/ water mixtures, and buffered aqueous solvents. Lenalidomide is more soluble in organic solvents and low pH solutions. Solubility was significantly lower in less acidic buffers, ranging from about 0.4 to 0.5 mg/mL. Lenalidomide has an asymmetric carbon atom and can exist as the optically active forms S(-) and R(+), and is produced as a racemic mixture with a net optical rotation of zero. Lenalidomide is available in 5 mg, 10 mg, 15 mg and 25 mg capsules for PO administration. Each capsule contains lenalidomide as the active ingredient and the following inactive ingredients: lactose anhydrous, microcrystalline cellulose, croscarmellose sodium, and magnesium stearate. The 5 mg and 25 mg capsule shell contains gelatin, titanium dioxide and black ink. The 10 mg capsule shell contains gelatin, FD&C blue #2, yellow iron oxide, titanium dioxide and black ink. The 15 mg capsule shell contains gelatin, FD&C blue #2, titanium dioxide and black ink.

### **9.2.2 Supply**

Lenalidomide (Revlimid) will come from commercially-available supply. Lenalidomide will be provided in accordance with Celgene Corporation's Revlimid REMS® program. Per standard Revlimid REMS® program requirements, all physicians who prescribe lenalidomide for research subjects enrolled into this

trial, and all research subjects enrolled into this trial, must be registered in, and must comply with, all requirements of the Revlimid REMS® program.

Lenalidomide will be shipped to the subjects' homes directly. If any unused drug is returned to the site by the subject it should be destroyed according to the local pharmacy's destruction policy

Further information about the Revlimid REMS® program is available at [www.celgeneriskmanagement.com](http://www.celgeneriskmanagement.com).

### **9.2.3 Storage Conditions**

Store lenalidomide at 25°C (77 °F) away from direct sunlight; excursions permitted to 15-30°C (59-86 °F).

### **9.2.4 Accountability**

Bottles of lenalidomide will contain a sufficient number of capsules to last for one cycle of dosing. Sites will be required to record and document subject compliance regarding lenalidomide dosing.

### **9.2.5 Prescribing Information**

Lenalidomide will be provided in accordance with the Revlimid REMS® program of Celgene Corporation. Per standard Revlimid REMS® requirements, all physicians who prescribe lenalidomide for research subjects enrolled into this trial must be registered in must comply with all requirements of the Revlimid REMS® program. Prescriptions must be filled within 7 days for females of childbearing potential and 14 days for all other risk categories. Only enough lenalidomide for one cycle of therapy will be supplied to the patient each cycle.

### **9.2.6 Special Handling Instructions**

Females of child-bearing potential should not handle or administer lenalidomide unless they are wearing gloves.

## **9.3 Dexamethasone**

Dexamethasone may be given IV or PO

### **9.3.1 Description**

Dexamethasone, a synthetic adrenocortical steroid, is a white to practically white, odorless, crystalline powder. It is stable in air. It is practically insoluble in water.

### **9.3.2 Formulation**

Dexamethasone is a commercially available PO drug, supplied as 2 and 4 mg tablets.

### **9.3.3 Storage Conditions**

Store dexamethasone at controlled room temperature 20 to 25°C (68 to 77°F)

### **9.3.4 Accountability**

Sites will be required to record and document subject compliance regarding dexamethasone dosing.

## **9.4 Daratumumab Subcutaneous Injection**

### **9.4.1 Description**

Daratumumab-SC will be provided as a fixed-dose (1800 mg), combination drug product containing rHuPH20 drug substance (2000 U/mL) and daratumumab drug substance (120 mg/mL) in a single vial.

### **9.4.2 Supply**

### **9.4.3 The daratumumab supplied for this study is manufactured by Janssen Biotech Inc. and provided under the responsibility of Janssen Scientific Affairs, LLC.**

Daratumumab must be stored in the original carton at controlled temperatures in a refrigerator ranging from 2°C to 8°C under the conditions outlined in the separate Pharmacy Manual. The product must be protected from direct sunlight and must not be frozen.

### **9.4.4 Accountability**

The Site Investigator will maintain records of each shipment of investigational product. The records will document shipment dates, method of shipment, batch numbers, and quantity of vials contained in the shipment. Upon receipt of the investigational product, the designated recipient at the study site will inspect

the shipment, verify the number and condition of the vials, and prepare an inventory or drug accountability record.

Drug accountability records must be readily available for inspection.

Empty and partially used vials should be accounted for and destroyed at the study site in accordance with the internal standard operating procedures. Drug destruction records must be readily available for inspection.

## **10 STATISTICAL CONSIDERATIONS**

### **10.1 Objectives**

#### **10.1.1 Primary Objective**

The primary objective of this study is to evaluate the rate of sCR and the rate MRD-negative disease by NGS at the end of 8 cycles.

#### **10.1.2 Secondary Objectives**

Secondary objectives include characterization of efficacy variables:

- Rate of MRD by next generation gene sequencing (NGS) by clonoSEQ (Adaptive Biotechnologies) at the end of Cycle 8 and at the end of cycle 24, and then yearly for as long no PD up to 2 years
- Duration of response (DOR), progression free survival (PFS), time to progression (TTP), and overall survival (OS)
- Overall response rate defined as partial response or better (>PR) including the rate of VGPR or better (>VGPR) and near complete response or better (sCR/CR/nCR) across entire treatment in high risk and low risk patients at indicated time points and as best response.
- Safety and tolerability of combination of D-KRD.

#### **10.1.3 Exploratory Objectives**

The exploratory objectives of this study are to conduct GEP, proteomics, RNASeq, and gene sequencing studies on pre-treatment patient samples to evaluate the correlation between treatment outcome and pre-treatment patient profile.

### **10.2.2 Primary Endpoint Analysis**

The primary objective of this study is to evaluate the rate of sCR and the rate MRD-negative disease by NGS at the end of 8 cycles. Time to sCR and MRD-negative response will be calculated from the date of first treatment on protocol. Subjects at the time of analysis not having either endpoint will be censored. Adherence to protocol and ability to follow patient in follow-up is expected to be excellent; however, if any patient revokes consent for the study not due to disease progression, they will be censored on their last clinical visit follow-up date. Likewise, patients in follow-up that are lost or that refuse or revoke study participation will be censored on their last clinical visit follow-up date.

Primary analysis will require 45 non-transplant candidates and/or transplant candidates who agreed to defer transplant to test the null hypothesis that the sCR and/or negative MRD status by NGS rate after 8 cycles is,  $\leq 30\%$  against the alternative that it is,  $> 30\%$  using an exact one-sided binomial test at the  $\alpha=0.10$  significance level. The null hypothesis will be rejected if 17 or more sCR's and/or MRD-negative's responses are observed ( $> 42.5\%$ ). The sample size of  $n=45$  response evaluable subjects provide a little over 85% power if the true sCR and/or negative MRD status rate by NGS is 50%. Based on this analysis, the study will provide preliminary estimate of probability of improvement of outcome of treatment with KRd w/o ASCT or with deferred ASCT for transplant candidates. In addition, we will conduct secondary analysis of sCR and/or MRD rates at the end of 8 cycles to test the null hypothesis that the sCR and/or negative MRD status by NGS rate after 8 cycles is,  $\leq 30\%$  against the alternative that

it is, >60% using an exact one-sided binomial test at the  $\alpha=0.10$  significance level. The sample size of  $n=45$  response evaluable subjects provide a little over 99% power if the true sCR and/or negative MRD status rate by NGS is 60%. Based on this analysis, the study will provide preliminary estimate of probability of similar efficacy of D+KRd to KRd+ASCT. The sample size is selected to also allow for collection of sufficient data for toxicity and tolerability evaluation of the D-KRd regimen. The frequency of adverse events will be summarized by type, grade, and attribution to the study drugs.

### **10.2.3 Secondary Endpoint Analysis**

The rate of MRD-negative disease by NGS will be reported at screening, 8, 12, 18, 24 months and then yearly until progression up to 5 years. Additionally, sites will be required to provide unstained pre-treatment slides to assess MRD by Adaptive. Comparison between D+KRd and historical KRd+ASCT rates will be made using a standard chi-square or Fisher's exact test. At the conclusion of the trial, with all subjects evaluated for PFS assessment at 5-years, the rate of MRD-negative status will be compared between D+KRd and historical KRd+ASCT data. This analysis will be conducted by contingency tables, or by adjusted logistic regression models, which will explore for any important confounders. Improvement of response during therapy measured at 6 and 12 months first treatment on protocol will be compared between D+KRd and historical KRd+ASCT data. Proportions of improving patients will be reported by treatment group, and comparisons of those proportions will be conducted using the chi-square or Fisher's exact tests. Overall survival will be calculated from date of first treatment on protocol until death from any cause and measured based upon the intention-to-treat paradigm, and will be compared between D+KRd and historical KRd+ASCT data using Kaplan and Meier survival models and the log-rank test statistic. In addition, all secondary endpoints will be tested for differences to historical controls using the one-sample log-rank test. The duration of MRD-negative disease will be calculated between the date of first occurrence of MRD-negative status, until such time as MRD-positive disease assessment or date of disease progression. Comparisons of duration of MRD-negative status may require the use of interval censoring methods. And finally, safety of the regimens will be assessed by comparing CTCAE Grade toxicity occurrence between D+KRd and historical KRd+ASCT data. Toxicity of Grade 2 and higher will be tabulated for each system organ class (SOC) and common individual toxicities occurring with SOC's reported. The maximum graded toxicity overall and within SOC will be reported per patient with the results summarized by treatment group and frequencies compared using chi-square tests or Fisher's exact tests as appropriate.

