|                                         | 
stem cell harvest. After completion of stem cell harvest, subjects will resume protocol treatment.
 
Subjects who complete 24 months of D-KRd will then proceed to lenalidomide single-agent maintenance at least tolerated dose on Days 1-21 in 28-day cycles.
 
All subjects will undergo testing for minimal residual disease (MRD) using next generation sequencing (NGS) using clonoSEQ with 10-6 sensitivity at the end of Cycles 8 and 24. After Cycle 24, testing will continue on a yearly basis for as long as the subject is free of progression for a maximum follow-up period of 2 years. If a CR is suspected after Cycle 8, subjects will undergo MRD testing at Cycle 12 and/or 18 as well.
                                                                                                                                                                                                                                                                                                                                                                                                                                                                                                                                                               |

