Minimal residual disease analysis will be performed using NGS. MRD will be assessed in all bone marrow samples at the beginning of the study (after Cycles 8 and 24), yearly until progression and at any time a bone marrow biopsy is completed to assess response for suspected CR. If a CR is suspected after Cycle 8, a bone marrow biopsy and MRD testing will be completed at Cycle 12 and/or 18 to confirm. From the time CR is established, MRD analysis should continue at 12-month intervals from randomization up to 5 years in patients with ongoing sCR. The MRD samples will be evaluated by Adaptive Biotechnologies using LymphoSIGHT® platform after isolation of DNA at the University of Chicago site. For this purpose (and to establish a baseline), sites will be required to provide unstained pre-treatment slides to assess MRD status by Adaptive Biotechnologies. MRD analysis will be used only for assessment of treatment response at specified timepoints, and not for decision-making purposes.

Treatment responses will be assessed by serum free light chains (SFLC), Hevylite test, quantitative immunoglobulin levels (Igs), and serum and urine monoclonal protein starting at Cycle 2 Day 1 and at the

beginning of each subsequent cycle. Subjects with stable disease or better will continue treatment until disease progression or the development of unacceptable toxicities. All patients will then undergo a final visit (end of treatment visit).

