| Myeloma Disease Assessment Laboratory                                                                                                                                      | M-protein determination: 
 
• Serum protein electrophoresis and immunofixation
 
• Urine protein electrophoresis and immunofixation
 
• Serum free light chains and Hevylite test
 
• Serum quantitative immunoglobulins
 
 Only those assessments used to follow the myeloma disease are required past screening. All assessments are required for confirmation of response. |
| Aspirate/Biopsy                                                                                                                                                            | All BM aspirates are SOC. Quantify percent myeloma cell involvement, and obtain bone marrow aspirate for MRD analysis by NGS. This is required at end of Cycle 8, 24 and confirmation of CR. If a CR is suspected after Cycle 8, a bone marrow biopsy and MRD testing will be completed at Cycle 12 to confirm. For subjects who sign consent for correlative                                                                                  |

|                                 |                                                                                                                               |
|---------------------------------|-------------------------------------------------------------------------------------------------------------------------------|
|                                 | samples, an additional aspirate sample should be collected at the time of the SOC BMA.                                        |
| CT-PET                   | A CT-PET must be performed to confirm MRD-negative disease per standard of care (SOC), at every timepoint when MRD is checked |
| Neurotoxicity Assessment | Including Neurotoxicity Questionnaire ( Appendix 5 )                                                          |
| QOL Assessment           | Patient reported survey ( Appendix 6 )                                                                        |
| Adverse Events           | Assessed on an ongoing basis                                                                                                  |

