31. One bone marrow sample for central Minimal Residual Disease (MRD) analysis by NGS at Adaptive Biotechnologies will be collected from all subjects: 1) screening (sample is required for calibration of MRD by gene sequencing. In the event that a superfluous bone marrow aspirate –BMA- sample from screening was not available, slides of BMA smear or clot from a time prior to enrollment can be used), 2) end of cycle 8, 3) end of cycle 24 (EOT), 4) 1 and 2 years after EOT for all subjects; 5) any time that a bone marrow is performed as SOC to assess CR response. If CR is suspected after cycle 8, the bone marrow biopsy/aspirate must be performed at the end of Cycle 12. For any bone marrow collected after Cycle 8 or Cycle 24, the visit may be done on Day 22-28 of that cycle.
32. A CT-PET will be performed to confirm MRD-negative disease per Standard of Care, at every time-point when MRD is checked (+/- 2 weeks). A bone marrow done as SOC 1 and 2 years after the EOT BM will be tested for MRD and a CT-PET done to confirm MRD-negative disease (+/- 2 weeks).
33. Local testing for hepatitis B surface antigen (HBsAg), hepatitis B surface antibody (Anti-HBs), and hepatitis B core antibody (Anti-HBc). HBV serology is not required at Screening if this was performed as part of standard of care within 3 months prior to first dose.
34. For subjects with serologic evidence of resolved HBV infection (i.e., positive Anti-HBs or positive Anti-HBc) at Screening, HBV DNA testing by PCR must be performed locally.
35. Q12W for up to 6 months after the last dose of study treatment.
36. If administered by subcutaneous (SC) injection, daratumumab will be provided as a fixed-dose of 1800 mg and 30,000 units hyaluronidase per 15 mL (120 mg and 2,000 units/mL) for all cycles. All subjects receiving daratumumab subcutaneous injection will be observed for at least 6 hours after the end of the SC injection during Cycle 1 Day 1 and, if deemed necessary by the treating investigator, after subsequent injections.
37. No provider patient visits will be held on Cycle 1, Day 22.

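### MRD-negative rates are planned at 12 and 18 months, but on-treatment sampling at those points depends on response, so the rates would describe a selected subset

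*Protocol*

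**What the plan says.** **Analysis.** Section 10.2.3 of the Protocol commits to this: "The rate of MRD-negative disease by NGS will be reported at screening, 8, 12, 18, 24 months", then yearly. No subset is named, so 12 and 18 have the same standing as 8 and 24. After a sentence about pre-treatment slides it continues: "Comparison between D+KRd and historical KRd+ASCT rates will be made using a standard chi-square or Fisher's exact test". That sentence gives no time point and no denominator.

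**Sampling of all subjects.** The Synopsis fixes who is tested ("All subjects will undergo testing for minimal residual disease (MRD") and when ("sensitivity at the end of Cycles 8 and 24. After Cycle 24, testing will continue on a yearly basis").

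**Conditional sampling.** The Synopsis adds: "If a CR is suspected after Cycle 8, subjects will undergo MRD testing at Cycle 12 and/or 18 as well". Section 4.1 has the same condition: "a bone marrow biopsy and MRD testing will be completed at Cycle 12 and/or 18 to confirm". It also provides MRD on any marrow taken for suspected CR, and at 12-month intervals in patients with ongoing sCR. Section 6.1.2 says of the MRD aspirate: "This is required at end of Cycle 8, 24 and confirmation of CR"; its conditional marrow is at Cycle 12 only. Section 7 likewise names only Cycle 12. The MRD footnote of Appendix 8 allows MRD on any marrow done to assess CR and then states: "If CR is suspected after cycle 8, the bone marrow biopsy/aspirate must be performed at the end of Cycle 12".

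**Objectives and endpoints.** Sections 2.2, 3.2 and 10.1.2 name Cycles 8 and 24 and yearly follow-up. They do not mention 12 or 18.

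**The concern.** Section 10.2.3 treats four on-treatment points as one series of rates, but the sampling plan supplies all-subject data at only two of them. At the other two, whether a patient has an MRD result depends on conventional response, which is closely tied to MRD status. A proportion among those tested is then a rate in a response-selected group.

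Two uses of the figures are at stake. Read as a series, 8, 12, 18 and 24 would show movements caused by changing denominators. Read against KRd+ASCT, a selected D-KRd subset would be set beside a historical rate. This matters because Section 1.7 makes comparability with KRd+ASCT a study hypothesis, and it quotes KRd+ASCT MRD results at the end of 18 cycles, so a Cycle 18 comparison is one that readers will look for. A later analysis plan can choose a denominator, but it cannot supply samples that were never scheduled.

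**Working it through.** The protocol gives no figure to reproduce here. The check sets the sections side by side and then illustrates the size with assumed inputs.

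**Step 1. Analysis points against sampling rules**

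| Protocol place | On-treatment sampling, all subjects | Sampling that depends on response |
|---|---|---|
| Synopsis | end of Cycles 8, 24 | suspected CR after Cycle 8: Cycle 12 and/or 18 |
| 4.1 | after Cycles 8, 24 | suspected CR: Cycle 12 and/or 18; any marrow for suspected CR; 12-month intervals in ongoing sCR |
| 6.1.2 | end of Cycles 8, 24 | confirmation of CR; suspected CR after Cycle 8: Cycle 12 |
| 7 | after 8 cycles, at 24 months | time of CR; suspected CR after Cycle 8: Cycle 12 |
| Appendix 8, MRD footnote | end of Cycles 8, 24 | any marrow to assess CR; suspected CR after Cycle 8: Cycle 12 |
| 10.2.3 (analysis) | reports 8, 12, 18, 24 | no condition stated |

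No section schedules MRD at 12 or 18 for everyone. So far as the Appendix 8 grid can be read, its MRD row has no mark in the Cycle 9-24 columns.

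**Step 2. Time scale.** Section 4.1.2.1 sets 28-day cycles. Months = cycles × 28 / 30.4375:
- 8 cycles: 224 days = 7.4 months
- 12 cycles: 336 days = 11.0 months
- 18 cycles: 504 days = 16.6 months
- 24 cycles: 672 days = 22.1 months

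The labels in 10.2.3 are therefore not those of the sampling plan. This is a minor point.

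**Step 3. Size, reading A: everyone with suspected or ongoing CR is tested.** N = 45 (Section 10.2.1). Let q be the share tested, a the MRD-negative rate among tested and b the rate among untested. All three are assumptions.

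All-patient rate = q·a + (1 − q)·b. Excess of the tested rate = (1 − q)(a − b).

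- q = 0.5, a = 0.8, b = 0.2: all-patient 0.50 against 0.80 among tested, an excess of 30 points.
- Smallest in the range run (q = 0.7, a = 0.7, b = 0.3): 0.3 × 0.4 = 12 points.
- Largest (q = 0.3, a = 0.9, b = 0.1): 0.7 × 0.8 = 56 points.

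For q from 30% to 70%, about 14 to 31 of 45 are tested.

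**Step 4. Size, reading B: only newly suspected CR is tested.** Let c be the share already in CR at Cycle 8, taken as 30% or 69% (the sCR rates that the protocol quotes for KRd without and with ASCT). Let n be the share of the rest newly suspected (assumed 20% or 50%). The assumed MRD-negative rates are a1 (newly suspected), a2 (already in CR) and b (neither).

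All-patient rate = c·a2 + (1 − c)·n·a1 + (1 − c)(1 − n)·b. Tested rate = a1.

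- c = 0.30, n = 0.2, a1 = 0.60, a2 = 0.85, b = 0.15: 0.255 + 0.084 + 0.084 = 0.423. Difference +18 points, with 45 × 0.70 × 0.2 ≈ 6 tested.
- c = 0.69, n = 0.5, a1 = 0.40, a2 = 0.90, b = 0.20: 0.621 + 0.062 + 0.031 = 0.714. Difference -31 points, with 45 × 0.31 × 0.5 ≈ 7 tested.

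Across the scenarios run, 3 to 16 of 45 are tested and the sign goes either way.

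**The case against.** Several stronger readings are tempting and the documents do not support them.

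- **Early responders are left out and only late converters are tested.** The trigger is a CR suspected after Cycle 8; the text does not say newly or first suspected. Section 4.1 also continues MRD at 12-month intervals in ongoing sCR, so some early responders may have a sample near month 12. The direction of bias therefore cannot be asserted.
- **Cycle 18 would be empty.** Sections 6.1.2 and 7 and Appendix 8 drop Cycle 18 from the conditional sample, but 6.1.2 and Appendix 8 still require MRD on a marrow that confirms or assesses CR. A CR suspected around Cycle 18 would be sampled.
- **The protocol specifies a test at 12 and 18.** The comparison sentence names no time point. Covering all the points just listed is the natural reading, but it is a reading.
- **The protocol fixes the wrong denominator.** It states none, and an analysis plan commonly does.

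It is also fair that 12 and 18 appear in no stated objective or endpoint, that the primary endpoint is untouched, and that months for cycles is loose usage found elsewhere in the protocol.

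Section 4.1 mentions yearly testing without a clear start, which might suggest a month-12 sample for all. The Synopsis starts yearly testing after Cycle 24, and Appendix 8 starts it after end of treatment.

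None of this removes the mismatch. Every extra on-treatment route to an MRD result still runs through response.

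**Conclusion.** The point holds in this form. Section 10.2.3 plans MRD-negative rates at 12 and 18 that the sampling plan can supply only for a response-selected subset. Such rates cannot be placed in series with Cycles 8 and 24, and a test of them against a whole-cohort KRd+ASCT rate would not be valid. The sections also conflict on Cycle 18.

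The size is illustrative: +12 to +56 points if all suspected or ongoing CRs are tested, and about -31 to +18 points if only new ones are. These figures rest on assumed testing shares and MRD rates, and on the tested patients being the denominator. That the historical rate is whole-cohort is also an assumption, since the protocol does not give its denominator. The mismatch itself needs none of these assumptions.

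This is a secondary analysis. It should be corrected, but it does not threaten the primary result.

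**What to change.** 1. In Section 10.2.3, report on-treatment landmark MRD-negative rates, and compare them with KRd+ASCT, only at end of Cycle 8 and end of Cycle 24. Label them in cycles and use all treated subjects as denominator.
2. Count subjects without a result as not MRD-negative, and apply the same rule to the historical data. Section 10.2.1 allows for unsuccessful MRD evaluation in up to 25% (about 11 of 45), so this rate will be conservative.
3. Name the historical time point set against Cycle 24. The KRd+ASCT regimen described in Section 1.7 ends at 18 cycles.
4. List Cycle 12/18 results descriptively with the number tested, and with no test against KRd+ASCT.
5. Keep any proportion of patients ever MRD-negative descriptive too, because responders are tested more often and have more chances of a negative result.
6. Reconcile the Cycle 12 and the Cycle 12 and/or 18 wording across the Synopsis, Sections 4.1, 6.1.2, 7 and 10.2.3, and Appendix 8.

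The cost is a wording change and the loss of two nominal time points that the sampling could not support. No extra marrow is needed.
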